## Abstract

**Background:**

Globally, traumatic brain injury (TBI) is recognized as one of the most significant contributors to mortality and disability. Most of the patients who have experienced TBI will be discharged home and reunited with their families or primary caregivers. The degree of severity of their reliance on caregivers varies. Therefore, the task of delivering essential care to the patients becomes demanding for the caregivers. A significant proportion of caregivers expressed considerable burden, distress, and discontentment with their lives. Therefore, it is critical to comprehend the dynamic of TBI and caregivers to optimize patient care, rehabilitation, and administration. The effectiveness of the Brain Injury Family Intervention (BIFI) program tailored for caregivers of patients with TBI has been widely proven in Western countries. However, the impact is less clear among caregivers of patients with TBI in Malaysia.

**Objective:**

This study aims to assess the effectiveness of BIFI in reducing emotional distress and burden of care, fulfilling the needs, and increasing the life satisfaction of caregivers of patients with TBI at government hospitals in Malaysia.

**Methods:**

This is a 2-arm, single-blinded, randomized controlled trial. It will be conducted at Hospital Rehabilitasi Cheras and Hospital Sungai Buloh. In total, 100 caregivers of patients with TBI attending the neurorehabilitation unit will be randomized equally to the intervention and control groups. The intervention group will undergo the BIFI program, whereas the control group will receive standard treatment. Caregivers aged ≥18 years, caring for patients who have completed >3 months after the injury, are eligible to participate. The BIFI program will be scheduled for 5 sessions as recommended by the developer of the module. Each session will take approximately 90 to 120 minutes. The participants are required to attend all 5 sessions. A total of 5 weeks is needed for each group to complete the program. Self-reported questionnaires (ie, Beck Depression Inventory, Positive and Negative Affect Schedule, Caregiver Strain Index, Satisfaction With Life Scale, and Family Needs Questionnaire) will be collected at baseline, immediately after the intervention program, at 3-month follow-up, and at 6-month follow-up. The primary end point is the caregivers’ emotional distress.

**Results:**

The participant recruitment process began in January 2019 and was completed in December 2020. In total, 100 participants were enrolled in this study, of whom 70 (70%) caregivers are women and 30 (30%) are men. We are currently at the final stage of data analysis. The results of this study are expected to be published in 2024. Ethics approval has been obtained.

**Conclusions:**

It is expected that the psychological well-being of the intervention group will be better compared with that of the control group after the intervention at 3-month follow-up and at 6-month follow-up.

**Trial Registration:**

Iranian Registry of Clinical Trials IRCT20180809040746N1; https://irct.behdasht.gov.ir/trial/33286

**International Registered Report Identifier (IRRID):**

RR1-10.2196/53692

## Introduction

### Background and Rationale

Traumatic brain injury (TBI) is defined as any injury sustained by the head as a result of blunt or penetrating trauma, acceleration or deceleration forces [1]. It remains as a leading cause of mortality and morbidity worldwide [2]. In Malaysia, despite investment in various preventive efforts, the incidence of TBI continues to increase yearly [3]. In 2009, as many as 166,768 trauma cases were recorded in 8 hospitals in Malaysia, most cases (76.8%) being road traffic accidents [4]. A recent study reported an extremely high cost of treatment for patients with TBI in Malaysia. The estimated annual cost of treatment for 49 patients with TBI was as high as MYR 1.5 million (US $313840) [5]. In the long term, this would lead to an adverse impact on the social and economic development of the country.

The effects of TBI depend largely on the severity and location of the injury and the age and personality of the patient [1]. TBI will affect their self-care ability, employment capacity, and social functioning. Upon discharge from hospitals, most patients with moderate to severe levels of TBI would need to move back in with their families to receive the care they need [6,7]. Patients with severe TBI are unlikely to return to their previous employment as they require a significant amount of care [8]. As most of the patients with TBI are highly dependent, their caregivers are tasked with providing the necessary physical care for them. The caregivers are also constantly involved in any ongoing rehabilitation of the patients, for example, encouraging them to perform physiotherapy exercises and reminding them to take medication. Moreover, the caregivers need to deal with difficult behaviors and challenging emotional states of patients with TBI [9-12]. These extra demands can be unfavorable to the health and well-being of the caregivers.

Many studies have highlighted the importance of understanding the dynamics of TBI on caregivers. There is an extensive body of research on the effect of TBI on caregivers globally [13-22]. However, local data are scarce, as only a few studies have been conducted to assess the effects of TBI on Malaysian caregivers [23-25]. The available studies have found that most TBI caregivers in Malaysia reported high burden and poor life satisfaction as a result of caregiving activities [25]. Similarly, there is also a lack of information regarding the needs of caregivers of patients with TBI in developing countries. It was suggested that caregivers of patients with TBI should be provided a postdischarge rehabilitation program to reduce their burden as caregivers [25]. A systematic review has suggested that caregivers of patients with TBI should be prioritized in TBI rehabilitation [26], as evidence abounds on the benefits of intervention programs tailored for caregivers toward patients with TBI [27-30].

In Malaysia, there is a lack of specific or structured intervention programs focusing on the psychological well-being of caregivers of patients with TBI. Identifying caregivers at an increased risk of burden is important for preventing emotional distress and caregiver burden to improve care for both patients and caregivers. Therefore, it is important to design a proper intervention plan to improve the quality of life of caregivers of patients with TBI. Ultimately, this will result in better care and management of patients with TBI.

### Conceptual Framework

This study is based on 2 major theories, namely, the Family System Theory (FST) and Cognitive Behavior Therapy (CBT) [31].

The first theory, FST, assumes that the whole family is interconnected to one another [32]. For instance, if a family member is affected by TBI, the whole family system will also be affected [31]. Patients with TBI would most likely depend on their family members for activities of daily living, routine follow-up, rehabilitation, and financial support. This would increase the burden on the caregivers. Family members would also need to look for coping resources to overcome their problems [13,33,34]. As a result of the sudden changes in the family’s functioning, family members often reported a lack of coping skills, in addition to high levels of burden, anxiety, and emotional distress [17,33,35-40], thus resulting in a decrease in psychological well-being [19,41-43]. Therefore, Brain Injury Family Intervention (BIFI) incorporates family therapy techniques such as normalization and validation to assist patients with TBI and their families.

The second theory, CBT, is widely known for its use in treating various types of psychological disorders [44]. Several studies have applied CBT to provide psychological interventions to patients with TBI and their caregivers [28,45-50]. A systematic review revealed that CBT has a significant impact on improving the psychological well-being of TBI caregivers [32,45]. CBT would equip caregivers of patients with TBI with strategies to deal with psychological problems such as depression and anxiety [44]. A specific component of CBT would also be implemented in BIFI that covers important aspects such as psychoeducation, problem-solving skills, management of emotions, setting of realistic goals and expectations, and stress management.

### Aims of This Study

This study aims to assess the effectiveness of BIFI in reducing emotional distress and burden of care, besides fulfilling the needs and increasing the life satisfaction of caregivers of patients with TBI in selected hospitals.

The hypotheses of this study are as follows:

There is a significant association between the sociodemographic and clinical characteristics of patients with TBI and the emotional distress, burden of care, needs, and life satisfaction of caregivers of patients with TBI.There is a significant difference in the mean scores of caregivers’ emotional distress, burden of care, needs, and life satisfaction between the intervention and control groups before the intervention, after the intervention, at 3-month follow-up, and at 6-month follow-up.The sociodemographic and clinical characteristics of the patients are predictors of the intervention outcomes.

## Methods

### Study Design

This is a 2-arm, single-blinded, randomized controlled trial (RCT). All participants will be randomly assigned to the intervention group or control group. Only the investigators will be aware of the treatment allocation.

### Study Setting

This study will be conducted at Hospital Rehabilitasi Cheras (HRC) and Hospital Sungai Buloh (HSB). These hospitals are the main referral hospitals for patients with TBI. A specific room in each site will be used for data collection. Figure 1 outlines the study flow according to CONSORT (Consolidated Standards of Reporting Trials) 2010.

**Figure 1 figure1:**
[figure not shown]
Research flowchart. BIFI: Brain Injury Family Intervention; TAU: treatment as usual.

### Participants

A total of 100 participants were recruited for this study. Of the 100 participants, 50 (50%) were randomly assigned to the intervention and control groups, respectively. All caregivers of patients with TBI who attend follow-up with patients with TBI at the Neuro Rehabilitation outpatient clinic of HRC and HSB were screened for eligibility to participate in this study.

### Inclusion and Exclusion Criteria

To be eligible, caregivers of patients with TBI must be citizens or permanent residents of Malaysia and be aged ≥18 years, regardless of their race, ethnicity, and sex. The participants must be able to read or write in Bahasa Malaysia or English. The caregivers can be the parents, spouses, siblings, sons or daughters, or relatives of the patients with TBI. Only 1 caregiver per patient with TBI can be recruited for the program. Time since injury for the patient with TBI must be >3 months and time spent on caring for the patients must be at least 2 hours per day. All types of injury severity were included. However, paid caregivers were excluded.

### Withdrawal Criteria

The participants may choose to withdraw at any point of time without any penalty. The participants may be withdrawn if the investigator believes that it is harmful or risky for the participants to continue.

### Sample Size Estimation

Sample size estimation is based on the formula for clinical superiority trial [51]:

N=2x (Z_1–α_ + Z_1–β_)^2^ × S^2^ / (δ–δ_0_).

The sample size is calculated with 80% power (Z_1–β_=0.845) at a significance level (α) of .05, with 95% CI (Z_1–α_=1.96), 25% dropout rate, and medium size effect of 0.60. The parameters used in the formula will be based on a previous study [45], including δ^2^=9.355 (pooled SD) and depression (Beck Depression Inventory [BDI] score) δ–δ_0_=5.86 (mean difference). According to the calculation, a total of 50 participants per arm will be needed for this study.

The parameter used to compute the prevalence of caregivers of patients with TBI was taken from the paper titled “Life satisfaction and strain among informal caregivers of patients with traumatic brain injury in Malaysia” [25].

### Sample Size Calculation for Prevalence Studies

In this formula, n=sample size, z=z statistic for the level of confidence, P=expected prevalence, and d^2^=allowable error. This formula assumes that P and d^2^ are decimal values but would also hold true if they are percentages, except that the term, 1–P, in the numerator would become 100–P [52]:

N=Z^2^
*P* (1–P) / d^2^

Percentage of caregiver’s burden=57.4%, level of significance=5%, power=80%, and d=0.05:

N=(1.96)^2^ 0.574 (1 – 0.574) / 0.05^2^

N=376

This study aimed to assess eligibility for at least 376 caregivers of patients with TBI.

### Allocation

#### Allocation Sequence Generation

Methods of random allocation are used to ensure that all study participants have the same chance of allocation to the treatment or control group. Caregivers of patients with TBI who are eligible and consent to participate will be number coded before randomization. A simple random sampling method using computer-generated random sampling will be used to assign participants to the intervention group or control group. The procedure would be performed by following the 1:1 allocation format. Randomization will be performed by the principal investigator. All participants will have equal chance of being assigned to the intervention or control group.

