### Statistical Analysis

Data analysis will be performed using SPSS software (version 24.0; IBM Corp). Descriptive statistics will be used to describe the characteristics of participants. Continuous data will be reported as means and SDs or as medians and IQRs. Categorical data will be reported as percentages and frequencies. The comparison of the means between the 2 groups will be performed using a paired samples 2-tailed *t* test. In addition, 1-way ANOVA and repeated measure ANOVA will be conducted to identify any significant differences in mean scores of emotional distress (BDI), caregiver’s needs (Family Needs Questionnaire [FNQ]), burden of care (Caregiver Strain Index [CSI]), and life satisfaction (Satisfaction With Life Scale [SWLS]) before the intervention, after the intervention, at 3-month follow-up, and at 6-month follow-up between the intervention and control groups. Multivariate regression analysis will be used to determine the predictors of intervention outcomes.

The intention-to-treat analysis will be performed accordingly. Assumptions of normality and homogeneity of variance will be conducted and adjusted where necessary.

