### Control Group

The control group or treatment-as-usual group will not receive any additional treatment during the study period. Participants in the control group will receive the usual treatment at their respective hospitals. According to the Malaysian Clinical Practice Guidelines for early management of head injury, all patients who have been discharged are recommended to attend follow-up sessions at the hospital [56]. It is recommended that patients with moderate and severe head injuries are scheduled for routine clinic follow-up. However, patients with a mild head injury can be followed up via clinic visits or telephone calls. Apart from the routine follow-up, other programs tailored for patients with TBI and their caregivers are also considered as treatment as usual in this RCT. For example, the Acquired Brain Injury Rehabilitation Unit in HRC would offer a program known as “Return to Work” for suitable patients and caregivers. A similar program is also available in HSB.

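### The stated between-arm tests adjust for neither the baseline score nor hospital, so avoidable chance imbalance and noise stay in the estimate

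*Protocol article*

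**What the plan says.** *Allocation.* The Allocation Sequence Generation section reads: "A simple random sampling method using computer-generated random sampling will be used to assign participants to the intervention group or control group". It adds "The procedure would be performed by following the 1:1 allocation format" and "All participants will have equal chance of being assigned to the intervention or control group". It mentions no blocks, batches or strata. The abstract plans that caregivers "will be randomized equally to the intervention and control groups", and the Participants section reports the result: "Of the 100 participants, 50 (50%) were randomly assigned to the intervention and control groups, respectively".

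*Hospitals.* Study Setting names two recruiting hospitals, HRC and HSB. Under Control Group, controls have the usual care of their own hospital, and "other programs tailored for patients with TBI and their caregivers are also considered as treatment as usual". HRC's Return to Work program is the example given, and the section says that HSB has a similar one. Under Contamination Bias, the intervention is held in a seminar room at the designated hospitals.

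*Analysis.* The Statistical Analysis section names a t test for the two-group comparison of means and says that "1-way ANOVA and repeated measure ANOVA will be conducted to identify any significant differences in mean scores" at the four assessments between the groups. A multivariate regression is planned, but to find predictors of outcome, not to estimate the arm difference. Hospital is named nowhere in the section, and the baseline score is not named as a covariate.

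*Timing.* The Results section says that recruitment has ended and data analysis is at its final stage. Anticipated Findings already reports a significant between-arm difference in distress after the program and at 3 months.

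**The concern.** Two facts known for every participant before the intervention, the recruiting hospital and the baseline score, could help explain later distress. The stated comparison uses hospital not at all and the baseline score only as one of the repeated measurements. With no stratification named, the hospital mix of the arms is left to chance. Any hospital difference in distress or in the surrounding care then enters the realised arm contrast in proportion to the imbalance, and variation that could be removed stays in the standard error.

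The baseline score is the more important of the two. A 1-way ANOVA or t test at one follow-up visit ignores it. A repeated measures ANOVA treats it as another outcome: the group main effect is then diluted by a time point at which no effect can exist, and the group-by-time contrast amounts to comparing changes from baseline. Neither is as precise as using the baseline score as a covariate.

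**Working it through.** **Inputs from the article:** 100 participants, 50 per arm; pooled SD 9.355 and mean difference 5.86 BDI points (Sample Size Estimation); 8-week test-retest correlations of 0.39–0.71 for negative affect and 0.47–0.68 for positive affect (PANAS Questionnaire). **Assumptions, because the article gives no figure:** the smaller hospital supplies H = 20, 30, 40 or 50 of the 100; the hospitals differ by 0.5 SD in BDI.

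**1. The plan's own figure.** 2 × ((1.96 + 0.845) × 9.355 / 5.86)² = 40.1 per arm, and × 1.25 = 50.1, which matches the stated 50. So the article's SD and difference can be used as the scale.

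**2. Chance imbalance in hospital mix.** With arms fixed at 50/50 and no stratification, the number X from the smaller hospital in one arm is hypergeometric(100, H, 50). The gap in hospital share is |2X − H| / 50.

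| H | P(gap ≥ 10 points) | P(gap ≥ 20 points) | SD of gap |
|---|---|---|---|
| 20 | 0.211 | 0.023 | 8.0 points |
| 30 | 0.275 | 0.049 | 9.2 points |
| 40 | 0.307 | 0.066 | 9.8 points |
| 50 | 0.317 | 0.071 | 10.1 points |

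Gaps move in steps of 4 points, so these tail probabilities depend on whether H is even or odd. Odd sizes tried between 21 and 49 give 0.33–0.42 for 10 points and 0.01–0.05 for 20. The SD of the gap is the steadier summary: 8–10 points throughout.

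**3. What a gap does to the contrast.** Shift = gap × 0.5 × 9.355.
- 10 points: 0.10 × 0.5 × 9.355 = 0.47 BDI points, 8% of 5.86.
- 20 points: 0.20 × 0.5 × 9.355 = 0.94 BDI points, 16% of 5.86.

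For scale, the unadjusted standard error is 9.355 × √(2/50) = 1.87.

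**4. Precision gained from hospital alone.** If 9.355 is the total SD and a share p comes from one hospital, hospital explains p(1 − p) × 0.5² of the variance.
- p = 0.5: 0.0625, so the standard error is multiplied by √0.9375 = 0.968, about 3% smaller.
- p = 0.8: 0.04, multiplied by √0.96 = 0.980, 2% smaller.

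**5. Precision gained from the baseline score.** With baseline-to-follow-up correlation r, ANCOVA multiplies the standard error of a follow-up-only comparison by √(1 − r²), and that of a change-from-baseline comparison by √((1 + r)/2). The article gives no r for BDI. Its PANAS range serves only as an illustration:
- r = 0.39: 0.921 and 0.834, that is 8% and 17% smaller.
- r = 0.71: 0.704 and 0.925, that is 30% and 8% smaller.

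These are 8-week correlations for another scale; those at 3 and 6 months may differ.

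**The case against.** **A condensed article need not list covariates.** This is true, and an analysis plan that is not shown may contain them. The absence of stratification is likewise inferred from silence. What stands is that the article does not leave the comparison open. It names the tests, and those tests are unadjusted. If an unseen plan already adjusts, only the article's wording needs aligning.

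**The hospital effect is small and assumed.** This also stands. The 0.5 SD has no source in the document, no hospital difference in distress is reported, and the similar program at HSB weakens any inference that usual care differs by site. Even on that assumption, one SD of imbalance (8–10 points) shifts the contrast by about 0.37–0.47 points, well inside a standard error of 1.87.

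**Repeated measures ANOVA already contains the baseline score.** It does, as one of the outcomes. The second multiplier in step 5 shows that this recovers only part of the gain.

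Two stronger readings are tempting. A reader might infer that 50 in each arm shows the allocation was not done as described. Coin-toss allocation of 100 gives exactly that split with probability C(100,50)/2¹⁰⁰ = 0.080, which is uncommon but no contradiction. Number-coded participants sampled in a 1:1 format could equally mean a fixed draw of 50 and 50, which forces it. A reader might also take the 0.94-point shift as bias. It is not: unstratified randomization is unbiased, chance imbalance is part of the random error, and 0.94 joins a 2–7% event to an assumed hospital effect.

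**Conclusion.** The point holds as one of precision and chance imbalance, not of validity. A model adjusting for baseline score and hospital is a better between-arm analysis than the tests the article states. For hospital the demonstrated benefit is modest: about a 21–32% chance of a gap of 10 points or more at the tabulated sizes, a shift of 0.47 BDI points at that gap, and a standard error 2–3% smaller, all resting on assumed hospital sizes and an assumed 0.5 SD difference. The baseline score probably brings more, but its size for BDI cannot be derived from the document. The exact 50:50 split is not evidence of an error; how it arose is a matter of wording only.

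**What to change.** Make the between-arm comparison a model of the post-baseline scores, either ANCOVA at each visit or a repeated-measures model over the three post-baseline visits, with arm as the effect of interest and the baseline score and hospital (HRC or HSB) as covariates.

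Because between-arm results have already been seen, report this model next to the analysis the article lists, and say that it was added after that look. It should not silently replace the listed analysis.

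As a clarification, add one sentence saying whether the 50:50 split was forced by blocks, batches or a fixed list, and whether allocation was done within hospital. Recruitment is complete, so the allocation itself can no longer be changed.

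The cost is about two degrees of freedom, one extra set of results and the disclosure. Both covariates should already be on file: the recruiting hospital and the baseline questionnaire.

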#### Blinding

The method of blinding in RCT is used to ensure that there are no differences in the way in which each group is assessed or managed and therefore minimize bias. In this study, only the principal investigator is aware of the treatment allocated to the participants.

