### Study Procedure

All the screening procedures to identify the participants based on inclusion and exclusion criteria were performed before the intervention program by rehabilitation physicians in the respective hospitals. The recruitment started in November 2018 and was continued until the required sample size was achieved. The BIFI program will be conducted in the Malay or English language depending on the needs of the caregivers. The participants in the intervention group will be divided into smaller groups of 10 people each. Each group will receive a scheduled time and date to attend the program at the hospital. The program will be conducted by the principal investigator, who is also a clinical psychologist. The clinical psychologist must at least have 5 years of experience.

At the baseline of the program (T1), all participants are required to complete the questionnaires (BDI, CSI, PANAS, FNQ, and SWLS). The same questionnaire will be distributed immediately after the intervention program (T2), at 3-month follow-up (T3), and at 6-month follow-up (T4). The average time needed to complete the questionnaire is 30 to 40 minutes. The follow-up sessions (T3 and T4) will be scheduled by the coinvestigators. The session will be conducted at the respective hospitals by the coinvestigators to prevent any bias during follow-up. The participants were also encouraged not to share the intervention materials with other caregivers until data collection is completed.

The intervention group will undergo the BIFI program. The BIFI program will be scheduled for 5 sessions as recommended by the developer of the module. Each session will take approximately 90 to 120 minutes. The participants are required to attend all 5 sessions. A total of 5 weeks is needed for each group to complete the program, and 2 groups will be scheduled every week. All the sessions will start with an overview of the topic and end with the summary and homework assignments. Participants will be required to complete the homework given according to the module. This homework will then be reviewed by the principal investigator in the subsequent session.

For the control group that receives the usual standard treatment, the caregivers will need to complete the questionnaires at similar time points as the intervention group.

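### The person who delivers BIFI also performs the randomization, and Table 1 places the self-reported baseline after allocation, while the data collection text can be read as placing it straight after consent

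*Protocol article*

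**What the plan says.** **Who assigns and who treats.** Allocation Sequence Generation: "Randomization will be performed by the principal investigator". Study Procedure: "The program will be conducted by the principal investigator, who is also a clinical psychologist".

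**How assignment is made.** "A simple random sampling method using computer-generated random sampling will be used to assign participants to the intervention group or control group". The ratio is 1:1, and entry comes before assignment: "Caregivers of patients with TBI who are eligible and consent to participate will be number coded before randomization".

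**Who knows the arm.** Blinding says that "only the principal investigator is aware of the treatment allocated to the participants". Study Design is wider: "Only the investigators will be aware of the treatment allocation". Data Collection and Time Frame describes the recruiting rehabilitation physicians as coinvestigators.

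**When baseline is taken.** Three places bear on this.

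- Table 1 ticks randomization under enrollment and allocation at time 0. BDI, PANAS, CSI and FNQ are first ticked at baseline t1, in the part of the schedule that follows allocation.
- Study Procedure ties T1 to the program: "At the baseline of the program (T1), all participants are required to complete the questionnaires".
- Data Collection and Time Frame goes from information sheet to reading time, signed consent and then the questionnaire. It does not mention randomization.

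All outcomes are self-reported. Statistical Analysis includes the pre-intervention score as one of the time points in the repeated-measures comparison.

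**The concern.** Two stated choices combine. First, the person who performs the randomization knows the allocation and has a stake in the program being tested. Second, on Table 1's order, caregivers report baseline distress once their arm has been set and possibly disclosed.

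Baseline is the reference for every change score and for the group-by-time term. Randomization makes the arms comparable at T1 only if T1 is measured before the assignment can influence the answers. A caregiver who has just been offered five group sessions, or none, may answer a mood questionnaire differently. Such a difference would be a reporting artefact at T1 that later looks like a treatment effect, or hides one.

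This bears on a claim already made. Anticipated Findings reports a significant reduction in emotional distress in the intervention group compared with control, and a reduction is measured from T1. Study Procedure has coinvestigators run the T3 and T4 sessions to guard against bias, but states no such safeguard for T1.

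**Working it through.** **Step 1: sequence of events.**

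| Source | Order stated |
|---|---|
| Allocation Sequence Generation | Eligibility, consent, number coding, randomization; T1 not mentioned |
| Table 1 | Randomization (enrollment), allocation (time 0), T1 questionnaires |
| Study Procedure | T1 at the baseline of the program |
| Data Collection and Time Frame | Consent, then questionnaire; randomization not mentioned |

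Table 1 is the only source that orders T1 against allocation explicitly, and it puts T1 second. Study Procedure is compatible with that. Data Collection and Time Frame reads most naturally as T1 in the consent sitting, which would put it before assignment, but it does not say so. The order is therefore not settled.

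**Step 2: would caregivers know their arm at T1?** Study Design and Blinding confine knowledge to the investigator or investigators. That cannot hold for long for people scheduled for, or left out of, five group sessions. No section says when caregivers are told.

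**Step 3: how a T1 shift would propagate.** Let δ be an arm-related shift in reported BDI at T1 that does not carry over to follow-up.

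- Change score, or a T1-versus-follow-up contrast in the group-by-time term: bias = δ in absolute size.
- Baseline-adjusted difference with slope r: bias = r × δ.
- Follow-up scores compared without baseline: bias from T1 = 0.

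For δ = 1 point (an assumption): the change-score bias is 1 point, and 1 / 5.86 = 17% of the planned difference. With r = 0.5 the adjusted bias is 0.5 point.

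**Step 4: range.** From the article: SD 9.355 and 50 per arm. Assumed: no true effect, equal SDs over time, shift b of 0.1 to 0.3 SD, and baseline-to-follow-up correlation r of 0.5 to 0.7 (which is also the slope when SDs are equal). In SD units, with √(2/50) = 0.2:

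- SE, adjusted = 0.2 × √(1 − r²)
- SE, change = 0.2 × √(2 − 2r)

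The two-sided 5% error is evaluated with the normal mean displaced by r × b / SE (adjusted) or b / SE (change).

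| b (SD) | δ (points) | r | Adjusted bias (points) | Error, adjusted | Error, change |
|---|---|---|---|---|---|
| 0.1 | 0.94 | 0.5 | 0.47 | 6.0% | 7.9% |
| 0.1 | 0.94 | 0.7 | 0.65 | 7.8% | 9.9% |
| 0.2 | 1.87 | 0.5 | 0.94 | 8.9% | 17.0% |
| 0.2 | 1.87 | 0.7 | 1.31 | 16.5% | 25.2% |
| 0.3 | 2.81 | 0.5 | 1.40 | 13.9% | 32.3% |
| 0.3 | 2.81 | 0.7 | 1.96 | 31.2% | 49.1% |

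This shows sensitivity only. It does not estimate what happened.

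**Step 5: direction.** If control caregivers report higher distress at T1 on learning their arm, their later scores look like improvement and the BIFI effect is understated. If intervention caregivers report higher distress at T1, the effect is overstated. The text does not favour either.

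**The case against.** The strongest reply is that nothing shows the baseline was contaminated. Data Collection and Time Frame can be read as consent followed at once by the questionnaire, and Table 1 may be a loosely filled template. That stands as far as it goes. A reader might infer that caregivers did know their arm when they gave baseline scores, but no section says so. What remains is that the one explicit ordering in the article is the unfavourable one.

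A reader might also infer that the principal investigator could choose who entered. The documents do not support this: rehabilitation physicians screen and recruit, and consent and number coding come before randomization. One gap is left, because the investigator who explains the study to caregivers is not distinguished from the principal investigator.

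Silence on envelopes or a central service is ordinary in a condensed article and is not held against the plan. Naming the person who delivers the intervention as the one who randomizes is a statement, not an omission.

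A reader might take the exact 50:50 split as a sign that simple randomization was not used. It is not: "The procedure would be performed by following the 1:1 allocation format", applied by sampling from number-coded caregivers, can mean drawing 50 of 100, which forces an even split. Unstratified simple randomization at two hospitals is also valid.

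Finally, the plan names no baseline-adjusted model and already lists between-group comparisons of mean scores, so the sensitivity analysis proposed here partly overlaps it. That makes it cheap. It does not make it redundant, because its role needs stating in advance of interpretation.

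**Conclusion.** The point holds as a risk built into the written plan and as an inconsistency to be resolved. It is not evidence that assignment was manipulated or that baseline scores were distorted. Two facts are stated outright: one person randomizes and delivers BIFI, and Table 1 places T1 after allocation. The timing of T1 is left unclear by Data Collection and Time Frame.

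If Table 1 describes what was done, any arm-related shift at T1 enters change and group-by-time results in full. Its size and direction are unknown. The 1-point (17%) figure and the error rates of about 6% to 31% with adjustment, or 8% to 49% for change scores, rest on assumed shifts and correlations. If T1 was completed before the arm was disclosed, the baseline part of the concern falls away and only the dual role remains to be reported.

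**What to change.** **Text.** Reconcile Table 1, Data Collection and Time Frame, and Study Procedure so that T1 is completed after consent and before the assignment is generated or revealed. Name an existing team member who neither recruits nor delivers BIFI to generate and hold the list. In a running trial this would cost a reordering of steps and the reassignment of one task.

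**This trial.** Recruitment is complete, so the conduct cannot be changed. Report who generated and held the list, and whether T1 preceded disclosure of the arm. If it did, correct Table 1.

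**If T1 did not precede disclosure.** Add a sensitivity analysis comparing follow-up scores between arms without baseline adjustment, and temper claims worded as change from baseline. No new data are needed. The downside is lower precision: compared with a baseline-adjusted analysis, the standard error grows by a factor of 1/√(1 − r²), which is 1.15 at r = 0.5 and 1.40 at r = 0.7 (assumed correlations). This analysis removes bias arising at T1. It does not remove any effect of knowing the arm on self-report at follow-up.
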